## Abstract

**Background:**

In patients with peripheral arterial disease (PAD), walking improvements are often limited by early pain onset due to vascular claudication. It would thus appear interesting to develop noninvasive therapeutic strategies, such as transcutaneous electrical nerve stimulation (TENS), to improve the participation of PAD patients in rehabilitation programmes, and thus improve their quality of life. Our team recently tested the efficacy of a single 45-min session of 10-Hz TENS prior to walking. TENS significantly delayed pain onset and increased the pain-free walking distance in patients with class-II PAD. We now seek to assess the efficacy of a chronic intervention that includes the daily use of TENS for 3 weeks (5 days a week) on walking distance in Leriche-Fontaine stage-II PAD patients.

**Methods/design:**

This is a prospective, double-blind, multicentre, randomised, placebo-controlled trial. One hundred subjects with unilateral PAD (Leriche-Fontaine stage II) will be randomised into two groups (1:1). For the experimental group (TENS group): the treatment will consist of stimulation of the affected leg (at a biphasic frequency of 10 Hz, with a pulse width of 200 μs, maximal intensity below the motor threshold) for 45 min per day, in the morning before the exercise rehabilitation programme, for 3 weeks, 5 days per week. For the control group (SHAM group): the placebo stimulation will be delivered according to the same modalities as for the TENS group but with a voltage level automatically falling to zero after 10 s of stimulation. First outcome: walking distance without pain. Secondary outcomes: transcutaneous oxygen pressure (TcPO_2_) measured during a Strandness exercise test, peak oxygen uptake (VO_2_ peak), endothelial function (EndoPAT®), Ankle-brachial Pressure Index, Body Mass Index, lipid profile (LDL-C, HDL-C, triglycerides), fasting glycaemia, HbA1c level, and the WELCH questionnaire.

**Discussion:**

TENS-PAD is the first randomised controlled trial that uses transcutaneous electrical therapy as an adjuvant technique to improve vascular function in the treatment of PAD. If the results are confirmed, this technique could be incorporated into the routine care in cardiovascular rehabilitation centers and used in the long term by patients to improve their walking capacity.

**Trial registration:**

ClinicalTrials.gov, ID: NCT02678403. Registered on 9 February 2016. Sponsor: Toulouse University Hospital.

**Electronic supplementary material:**

The online version of this article (doi:10.1186/s13063-017-1997-1) contains supplementary material, which is available to authorized users.

## Background

Peripheral arterial disease (PAD) is characterised by narrowing of the arteries feeding the lower limbs (subdiaphragmatic aorta, iliac arteries, lower-limb arteries) [1, 2]. PAD causes a loss of haemodynamic load, with or without clinical manifestations. The most reliable sign is the fall in the Ankle-brachial Pressure Index (ABI). The severity of the disease is assessed using the Leriche-Fontaine classification (Table 1).

**Table 1 Tab1:** Leriche-Fontaine classification of peripheral arterial disease (PAD)

Stage 1	Asymptomatic PAD. Absence of one or several peripheral pulses with no functional repercussions
Stage 2	Symptomatic PAD. Intermittent claudication manifesting as pain on walking, signs of muscle ischaemia on effort. ‘Mild’ intermittent claudication (stage 2a) if the walking distance is greater than 200 m or ‘severe’ (stage 2b) if the walking distance is less than 200 m
Stage 3	Severe PAD pain in the lower limb appearing at rest or in decubitus, a sign of permanent tissue ischaemia
Stage 4	Presence of trophic disorders or necrosis in the lower limbs, such as ulcers or gangrene, and indication of severe ischaemia in most cases leading to amputation

The prevalence is estimated at 2.2% and 1.2% in men and women older than 55 years, respectively, and substantially increases with age [3] up to 40% for both sexes after age 80 years [4, 5] and is associated with an excess risk of cardiovascular death [6]. According to the international REduction of Atherothrombosis for Continued Health (REACH) registry [7], 50% of PAD patients have polyvascular disease. On average, half of all patients will die within the 5 years following diagnosis [8, 9].

Vascular rehabilitation is principally based on walking, on the therapeutic education of the patient and on adapted gymnastics (American College of Cardiology Foundation/American Heart Association (ACCF/AHA) guideline recommendations 2013) [10, 11]. This must be implemented in conjunction with medical treatment at the claudication stage (stage 2) before considering revascularisation [1, 10]. To optimise reconditioning to effort, it is recommended to alternate phases of exercise during which the patient must walk until the pain threshold is reached (pain occurs just before onset of the claudication) followed by a 10-min phase of passive recovery [12]. Several randomised studies have shown that physical exercise based on walking significantly improved walking distance and walking speed, as well as participation in physical activities [13–17]. A recent Cochrane meta-analysis [18] showed that in 1816 PAD patients supervised physical exercise on a treadmill improved walking distance in patients from 50 to 200%, maximal walking time by 4.51 min (95% CI 3.11–5.92) and the distance walked by 108.99 m (95% CI 38.20–179.78) compared with classical medical management without physical exercise. Nonetheless, physical exercise did not improve the ABI (mean difference 0.05, 95% CI 0.00–0.09).

Despite the undeniable benefits of walking, this approach is very often limited by pain, which is felt relatively early, leading patients to stop walking after a few minutes and to have to rest for 5 to 10 min until discomfort/pain ceases before starting again. In addition, given this peripheral limitation, exercise intensity, and thus demand on the cardiovascular system, is often insufficient to obtain the global impact of reconditioning to effort which, therefore, remains relatively ineffective.

It therefore seems pertinent to develop new techniques as an addition to the classical methods for physical reconditioning in these patients. By decreasing pain and improving comfort, and thus walking potential in PAD patients, it should be possible to reach high enough levels of energy expenditure to have an impact on both central and peripheral aspects of physical reconditioning.

The effects of electrical stimulation on the lower limbs in PAD patients have been studied by Loubser et al. who reported vasodilatation in the affected leg after a single 60-min session [19]. In this study, the authors used neuromuscular electrical stimulation (NMES) at a frequency of 2 Hz, which induced twitches of muscle contraction as well as sensory stimulation. In a fairly similar protocol, a slight improvement in pain-free walking distance was reported [20]. Transcutaneous electrical nerve stimulation (TENS) is another type of electrical programme, which, unlike NMES, only induces sensory stimulation and is mainly used for its analgesic effect. In PAD patients, there are no data concerning the vasodilatory effect of TENS. However, a pilot study on the efficacy of a single session of TENS to the legs in the PAD patients before they walked on a treadmill was recently conducted by our team [21]. In this study, 15 stage-II PAD patients underwent 45 min of TENS previous to a standardised walking exercise on a treadmill. The TENS sessions were carried out in different experimental conditions: 10 Hz, 80 Hz, SHAM (presence of electrodes without stimulation), or CON (without electrodes). The results for walking in the low-frequency TENS group (10 Hz) were better than those in the other groups (*p* < 0.0003). No adverse effect was reported. These results suggest that a single session of 10-Hz TENS just before the walking exercise increases both the pain threshold and the walking distance in stage-II PAD patients.

We therefore hypothesised that the use of TENS in PAD patients would improve walking distance via its impact on two aspects of vascular claudication (reduced vascular flow and pain). This therapeutic technique has, nonetheless, never been used in routine cardiovascular rehabilitation. Based on our experience with TENS, we now wish to evaluate the efficacy of this technique in a chronic setting including a 45-min daily session, 5 days a week for 3 weeks, associated with a physical reconditioning protocol classically used in these patients.

## Methods/design

### Study design

The TENS-PAD study will be a prospective, double-blind, multicentre, randomised, placebo-controlled trial. Outcomes will be assessed before and after 3 weeks of a cardiac rehabilitation programme. The study protocol has been developed based on the Standard Protocol Items: Recommendations for Interventional Trials (SPIRIT) guidelines (Additional file 1). The trial is founded by the ‘Programme Hospitalier de Recherche Clinique’ (PHRC) supported by the French Ministry of Health and was approved by the Sud-Ouest Outre-Mer Committee for the Protection of Personnes and the Agence Nationale de Sécurité du Médicament et des Produits de Santé (2015-A01534-45). The promotor of the study is the Centre Hospitalier Universitaire de Toulouse. The study was registered at ClinicalTrials.gov (ID: NCT02678403).

Figure 1 shows the flow chart indicating the patient inclusion, parameter measurement and follow-up process for the trial. The SPIRIT figure (Fig. 2) provides an overview of the study conduct, review, reporting, and interpretation, and the populated SPIRIT Checklist is presented in Additional file 1. The final report will follow the Consolidated Standards of Reporting Trials (CONSORT) guidelines, as well as the Template for Intervention Description and Replication (TIDieR).

**Fig. 1 Fig1:**
[figure not shown]
Flow chart for patient inclusion and follow-up, showing screening, inclusion measurements, randomisation, and tests at follow-up. ABI (Ankle-Brachial Index) ; PAD (Peripheral Artery Disease); TcPO2 (Transcutaneous Oxygen Pressure) ; TENS (Transcutaneous Electrical Nerve Stimulation) ; TG (Triglyceride) VO2peak (Oxygen consumption at peak exercise) ; WELCH (Walking Estimated Limitation Calculated by History)

**Fig. 2 Fig2:**
[figure not shown]
Standard Protocol Items: Recommendations for Interventional Trials (SPIRIT) figure

### Participants

A total of 100 participants (aged from 18 to 85 years) admitted to a cardiovascular rehabilitation unit will be included in this study. Patients are eligible if (1) they present unilateral PAD (Leriche-Fontaine stage II) diagnosed by an angiologist who has previously performed a detailed arterial lesion description using an arterial Doppler ultrasound of the lower limbs, completed by microcirculatory assessment and showing an ABI ≤0.9, (2) they are able to take part in an outpatient rehabilitation programme, and (3) they are clinically stable. Participants will be excluded if they have (1) walking disorders related to orthopaedic or neuromuscular disease, (2) myopathy, (3) associated progressive disease causing deterioration in general health, or (4) an implanted pacemaker or defibrillator. All the inclusion and exclusion criteria are presented in Table 2.

**Table 2 Tab2:** Inclusion and exclusion criteria

Inclusion criteria	Unilateral Leriche-Fontaine stage-II PAD, admitted to a cardiovascular rehabilitation unit Men or women Aged 18 to 85 years Able to take part in an outpatient rehabilitation programme Clinically stable Sedentary Provided informed consent to participate in the study
Exclusion criteria	Age >85 years Ward of court Walking disorders related to orthopaedic or neuromuscular disease Participation in a structured physical reconditioning programme in the month before the study Renal insufficiency requiring dialysis Known and documented myopathy Progressive cancer Associated progressive disease causing a deterioration in general health Participation in another research protocol Skin disorder making it impossible to use TENS Absolute contraindication to physical activity Presence of a pacemaker/defibrillator

*PAD* peripheral arterial disease, *TENS* transcutaneous electrical nerve stimulation

### Study procedure

Patients will be identified and recruited by the investigators in one of the four centres taking part in the study: le Centre Hospitalier Universitaire de Toulouse (France), la Clinique de Saint-Orens (France), le Centre Hospitalier Universitaire de Dijon (France), and le Centre Hospitalier Universitaire de la Réunion (French overseas territory). Patients will be informed about the study and asked for their participation. If they agree, they will be invited to sign the informed consent. After baseline assessment, they will be randomised into two groups (TENS versus SHAM). The duration of participation is 3 weeks. After the end of the cardiac rehabilitation programme all the participants will be re-evaluated.

In this trial, we will not modify the medical treatment that could interact with the walking capacity of the patient during the protocol, notably vasodilators, vasoconstrictors, antiplatelet drugs, and analgesics.

### Exercise intervention

#### ‘TENS’ group

TENS consists in delivering electrical stimulation to the affected leg via two channels and four electrodes placed on the triceps surae and the quadriceps muscles. Electrical stimulation characteristics will be: 10-Hz frequency, symmetrical compensated rectangular biphasic pulses (200 μs), maximal intensity just below the pain threshold, 45 min per day, in the morning 1 h before the exercise, 15 sessions spread over 3 weeks.

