### Blinding and randomisation

The study participants will be randomised into two balanced groups (1:1): (1) TENS and (2) SHAM. The randomisation will be stratified according to the four inclusion centers, and the two arms (TENS and SHAM) will be distributed in random-sized blocks (blocks of 2, 4 or 6). The method of randomisation used will be Ralloc on stata 9.2 S.E.

The assessor executing the measurements and the investigators will be blinded to group allocation. The statistician will be blinded until completion of the statistical analysis. Only the physiotherapists executing the cardiac rehabilitation programme will be aware of the assigned group of randomisation. Physiotherapists will not participate to the baseline or final measurements.

Participants will be blinded regarding the randomisation group to which they belong. The physiotherapists will install the TENS device and electrodes and will programme the TENS unit (pulse width, frequency, and intensity) according to the TENS or SHAM group (using a current that automatically switches off after a few seconds of stimulation).

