Our team studied the effects on TENS on muscle sympathetic nerve activity (MSNA) in chronic heart failure (CHF) [35]. According to the results of our study, both TENS and neuromuscular electrostimulation (NMES) are able to reduce MSNA compare to sham stimulation (63.5 ± 3.5 versus 69.7 ± 3.1 bursts/min, *p* < 0.01 after TENS and 51.6 ± 3.3 versus 56.7 ± 3.3 bursts/min, *p* < 0.01 after NMES), suggesting that TENS to the lower limbs could inhibit sympathetic outflow directed to the legs in CHF patients and could be able to reduce vasoconstriction. In PAD, oxidative stress and reduced blood flow to working muscles induce the augmented blood pressure response to exercise caused by an exaggerated exercise pressor reflex (PR) [36–38]. The PR is a neurological reflex that increases sympathetic nervous system activity, constricts arterioles and increases blood pressure. It is well known that TENS treatment releases endogenous opioids in the central nervous system and produces analgesia [39–41]. Furthermore, it has been shown in previous animal studies that the stimulation of opioid receptors of group-III and -IV afferent endings contributes to attenuating the exaggerated exercise PR observed in rats with ligated femoral arteries [38, 42, 43]. Thus, according to our hypothesis, TENS could be a new technique to reduce sympathetic nerve activity, the PR, and to induce a neuromodulation of the vascular tonus in PAD in addition to its traditional direct analgesic effects. This easy-to-use therapeutic tool could prove to be extremely interesting as it is easy to transport for use at home so that patients can use it to complement daily walking exercise. In the long term this could be useful in discouraging a sedentary lifestyle and will hopefully guarantee a higher level of physical activity and thus have an impact on secondary prevention after PAD.

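### The protocol sets two different intensity ceilings for active TENS, and the one in the treatment section does not rule out muscle contraction

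*Protocol article*

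**What the plan says.** The Abstract (Methods/design) gives the active-arm ceiling as "maximal intensity below the motor threshold". The section that specifies the treatment (Exercise intervention, 'TENS' group) gives it as "maximal intensity just below the pain threshold", with "four electrodes placed on the triceps surae and the quadriceps muscles". The other stimulation settings agree in the two places: 10 Hz, 200 μs biphasic pulses, 45 minutes a day, 15 sessions over 3 weeks.

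The Background says that TENS, "unlike NMES, only induces sensory stimulation". It describes the earlier NMES study as using 2 Hz stimulation, "which induced twitches of muscle contraction as well as sensory stimulation".

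Under Blinding and randomisation, the physiotherapists "will programme the TENS unit (pulse width, frequency, and intensity") according to the allocated group. No ceiling is given there.

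The sham description also differs. The current stops after 10 s in the Abstract and after 5 s in the 'SHAM' group section. Blinding and randomisation gives no exact time.

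**The concern.** Intensity is the one stimulation setting defined by a patient's own threshold and not by a fixed number, so the written ceiling determines the dose. The motor threshold and the pain threshold are different limits. Titrating upward until just short of pain is a different instruction from staying short of contraction.

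What is at stake is the identity of the tested treatment. The trial's hypothesis concerns TENS as the Background defines it, and the absence of contraction is what separates it from NMES. The article itself presents NMES as possibly active. After the NMES study it adds: "In a fairly similar protocol, a slight improvement in pain-free walking distance was reported". That outcome is close to this trial's primary one. The Discussion also reports that "both TENS and neuromuscular electrostimulation (NMES) are able to reduce MSNA" (muscle sympathetic nerve activity), although in patients with chronic heart failure. If the 'TENS' group wording is followed and muscles contract, a difference from sham would be a real treatment difference but could not be credited to sensory TENS. Physiotherapists in four centres could also deliver different treatments while each follows one of the two texts.

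**Working it through.** **1. The two rules side by side.** For a given patient, let M be the motor threshold, P the pain threshold and I the current used.

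| Source | Rule |
|---|---|
| Abstract | I < M |
| 'TENS' group section | I just below P |

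- If P is at or below M, a current just below P is also below M, so it meets both rules.
- If P is clearly above M, a current just below P exceeds M. It obeys the 'TENS' group section, breaks the Abstract's limit, and produces the contraction that the Background assigns to NMES.

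The two rules therefore conflict in every patient whose pain threshold is clearly above the motor threshold. The article gives no data on M or P and adds no rule against visible contraction to the treatment section.

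**2. Which text fits the trial's own concept.** The Background's sensory-only definition agrees with the Abstract. The 'TENS' group section is the only one of the three without a motor limit or a sensory-only description, and it is the one that specifies the treatment.

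**3. How much of the treatment is covered.** The arm size is the protocol's own figure (Sample size calculation and statistical analysis), and it reproduces:

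- n per group = 2 × (1.960 + 1.282)² × (105/75)² = 2 × 10.51 × 1.96 = 41.2, rounded up to 42
- with 15% early exit: 42/0.85 = 49.4, rounded up to 50

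Planned active sessions: 50 × 15 = 750. If only 42 patients completed treatment, those completers would account for 42 × 15 = 630.

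Let q be the share of sessions in which a current just below pain exceeds the motor threshold. The article does not give q, so it can only be shown as an assumption:

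| q (assumed) | Sessions with contraction, of 750 |
|---|---|
| 0 | 0 |
| 0.5 | 375 |
| 1 | 750 |

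No effect on power or on the treatment difference follows from this, because neither q nor the added effect of contraction is known.

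**4. The sham times.** One session is 45 × 60 = 2,700 s.

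| Switch-off | Share of a session | Total over 15 sessions |
|---|---|---|
| 5 s | 5/2,700 = 0.19% | 75 s |
| 10 s | 10/2,700 = 0.37% | 150 s |

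The total session time is 15 × 2,700 = 40,500 s. As a dose the difference is negligible. It matters only for describing one reproducible sham.

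**The case against.** The strongest reply is that the harm depends on something the article never states: that a current just below pain would contract the muscle in these patients at these settings. The figure of 750 sessions is a headcount, not a measured impact. The section in question is headed TENS, the Background defines TENS as sensory, and the Abstract gives the motor limit, so a reader can recover the intended modality and take the pain limit as a comfort limit within it. The sympathetic-activity data come from heart failure and show similar falls with TENS (69.7 − 63.5 = 6.2 bursts/min) and NMES (56.7 − 51.6 = 5.1), so they do not show that contraction would add to the TENS effect. Finally, this is an article condensing a full protocol that is not shown, and the physiotherapists may work from a document without the conflict.

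Much of this stands as a limit on the consequence. The frequency of contraction is unknown, the supporting evidence is modest, and the sham discrepancy adds no weight. The conflict itself remains. This is not a detail left to a fuller document: the article states the setting twice and gives two different limits. An inference from the word TENS is a poor substitute for a limit when the treatment section states a different one explicitly.

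**Conclusion.** The concern holds. The article gives two incompatible ceilings for the active treatment, and the one in the treatment section does not secure the sensory-only stimulation that the trial sets out to test. This rests on the text alone. It does not assume that the pain threshold always lies above the motor threshold, only that the treatment section sets no motor limit, which is so.

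The conflict applies to every planned active session. The number in which it would change what is delivered could lie anywhere from none to all. The TENS-versus-SHAM comparison stays validly randomised, and the sample size and covariance analysis are untouched. The possible loss is in attributing a positive result to sensory TENS and in delivering the same treatment across four centres. It should be fixed before recruitment. The sham timing is a secondary correction.

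**What to change.** In the 'TENS' group section, replace the pain-threshold wording with a sensory-level intensity below the motor threshold, with no visible contraction. This matches the Abstract and the Background's definition of TENS. If titration to just below pain is what the investigators intend, correct the Abstract and the sensory-only description in the Background instead, so that the treatment is described as one that may contract muscle.

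In the same revision, give one sham switch-off time in the Abstract and the 'SHAM' group section: the one the device actually uses.

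The cost is a few words. The Trial status section says recruitment has not begun, so no patient would have been treated under the old wording. If the approved full protocol carries the same conflict, it would need a matching amendment. Nothing changes in sample size, randomisation or analysis.
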